### Recruitment

Research staff will identify potential participants via the Institution’s computerized appointment system. We will approach potential participants during their initial RT consult or RT simulation visits (prior to starting RT), screen them for eligibility, and ask them for consent. If a patient’s caregiver is not present during the initial contact, we will ask the patient for permission to contact the caregiver via telephone to obtain consent.

### Randomization

Dyads will be randomized using minimization [79], which is similar to stratified randomization in that participant characteristics are used to assign participants to a study condition. However, minimization results in better group balance and does not suffer from some of stratification’s limitations (e.g., increased probability of group imbalance when stratifying across several characteristics). Factors will include patient and caregiver sex and age and patient tumor grade (LGG; HGG) and KPS (100; 90; 80).

### Blinding

This will be an unmasked trial. However, research staff involved in data collection will be blind to group allocation.

### Data collection

Dyads in all three groups will be assessed at three time points: baseline, 6 weeks later, and 3 months later. All assessments are collected via online surveys (Redcap).

### Statistical methods

To evaluate our study aims and determine whether the DY and CY interventions should be further evaluated in a subsequent larger trial, we will follow the steps described below.

#### Specific aim 1

The primary objective of this research is to determine feasibility according to overall accrual, attrition, completion of questionnaires, and session adherence. We will calculate rates, frequencies, and 90% confidence intervals when applicable and judge the trial to be feasible if at least 50% of eligible dyads consent to participate (i.e., approach 150 couples to accrue 75). Moreover, we will deem the trial feasible if at least 70% of enrolled dyads (≥ 54) are retained and complete all follow-up assessments and on average at least 50% of all practice sessions are attended.

#### Specific aim 2

We will perform descriptive analyses of symptoms and QOL measures for patients and their FCGs, including calculations of means, standard deviations, and confidence intervals.

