**Methods:**

Seventy-five glioma patients undergoing radiotherapy and their family caregivers are randomized to the DY, CY, or a WLC group. Patient-caregiver dyads in the DY group and caregivers in the CY group receive 15 sessions (45 min each) over the course of patients’ standard radiotherapy (6 weeks). Patients and caregivers in all groups complete baseline assessments of symptoms, quality of life (QOL), and health utilization outcomes prior to randomization. Follow-up assessments are performed 6 weeks and then again 3 months later. The primary outcome is feasibility (i.e., ≥ 50% of eligible dyads consent, ≥ 70% of enrolled dyads complete all assessments, and ≥ 50% of all practice sessions are attended). We will also perform primarily descriptive analyses of the self-reported outcomes (e.g., fatigue, overall QOL) and explore potential intervention moderators (e.g., performance status) to inform a larger future trial.

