### Eligibility

#### Inclusion criteria

Both family caregiver (e.g., spouse/partner, parent, adult child, sibling) and patient must be willing to participate in this study and must be (1) at least 18 years old, (2) able to read and speak English, and (3) able to provide informed consent. Patients must be (1) diagnosed with primary malignant glioma, (2) scheduled to undergo daily RT for 6 weeks, and (3) have a Karnofsky Performance Status (KPS) of 80 or more.

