
### Sample size and sample size considerations

We will randomize 75 dyads to either the DY intervention, CY, or WLC groups (25 dyads per group). Based on Whitehead et al.’s (2016) recommendation, a pilot trial of 25 participants per group will detect a small standardized effect size with 90% power and two-sided 5% significance [74]. Of note, this trial is not designed to examine intervention efficacy, and we have not carried out any formal power calculations. In line with recommendations in the literature, we focus on examining feasibility and descriptive analyses [75–77]. Moreover, a sample size of 75 dyads is consistent with previously published psycho-oncological feasibility trials, in which the investigators typically enrolled 20–25 participants/dyads per study group [78].

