### Trial status

Participant recruitment started on May 2018 and is expected to be finished by April 2020.

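### Specific aim 1 names accrual as a feasibility dimension but judges it only by a consent percentage, which does not register how many dyads are enrolled or how fast

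*Protocol article*

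**What the plan says.** Under Statistical methods, Specific aim 1, the primary objective is to "determine feasibility according to overall accrual, attrition, completion of questionnaires, and session adherence". The decision rule then has three parts:

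- **Consent:** the investigators will "judge the trial to be feasible if at least 50% of eligible dyads consent to participate (i.e., approach 150 couples to accrue 75".
- **Retention and completion:** "at least 70% of enrolled dyads (≥ 54) are retained and complete all follow-up assessments".
- **Attendance:** "on average at least 50% of all practice sessions are attended".

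The Methods paragraph of the abstract gives the same three thresholds: "≥ 50% of eligible dyads consent, ≥ 70% of enrolled dyads complete all assessments, and ≥ 50% of all practice sessions are attended". Neither place gives a number of dyads per month or a date by which the target must be reached.

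The target is under Sample size: "We will randomize 75 dyads to either the DY intervention, CY, or WLC groups (25 dyads per group". The only time frame for recruitment is under Trial status: "Participant recruitment started on May 2018 and is expected to be finished by April 2020". It is stated as an expectation, and the decision rule does not refer to it.

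**The concern.** The opening of Statistical methods says that these steps determine whether the interventions should go forward to a larger trial. Planning such a trial needs two different quantities: how willing eligible dyads are to join, and how many can be enrolled in a given time. The consent percentage measures the first only. The other two criteria are computed among dyads already enrolled, so, read as percentages, they do not measure the second either. The dimension that the aim names first therefore has no criterion that responds to the number or pace of enrolments.

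The consequence also shows in the Discussion. If the criteria are not met, the sponsor will open the trial to dyads at later points in the treatment trajectory. That remedy enlarges the pool of eligible dyads, yet no criterion measures the pool. Slow enrolment among willing dyads would not by itself trigger it.

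**Working it through.** **Inputs.** Target 75 dyads (Sample size). Consent threshold 50%, illustrated as 75 from 150 (Specific aim 1). Retention threshold 70%, with a count of 54 (Specific aim 1). Recruitment window May 2018 to April 2020 (Trial status), which is 24 months counted inclusively or 23 month to month.

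**Step 1. The plan's own figure.** 0.50 × 150 = 75 and 75 / 0.50 = 150. The consent illustration reproduces.

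**Step 2. Pace implied by the window.** 75 / 24 = 3.125, about 3.1 dyads randomized per month; over 23 months, 75 / 23 = 3.26, about 3.3. At 50% consent, 150 / 24 = 6.25 eligible dyads per month.

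**Step 3. The criteria when pace varies.** The documents give no site volume, so the number of eligible dyads per month is an assumption, shown as a range. Consent is held at 50%. Enrolled by month 24 = eligible per month × 0.50 × 24. Months to reach 75 = 75 / (eligible per month × 0.50).

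| Eligible per month (assumed) | Enrolled per month | Months to 75 | Enrolled by month 24 | Consent rule | 70% of those enrolled by month 24 | 54 retained possible at month 24? |
|---|---|---|---|---|---|---|
| 6.25 | 3.1 | 24 | 75 | met | 52.5, so 53 | yes |
| 5.0 | 2.5 | 30 | 60 | met | 42 | only with 54/60 = 90% retained |
| 4.2 | 2.1 | 36 | 50 | met | 35 | no |
| 3.1 | 1.6 | 48 | 37.5 | met | 38 enrolled: 26.6, so 27 | no |
| 2.5 | 1.25 | 60 | 30 | met | 21 | no |

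The consent rule is met in every row because pace cancels out of the ratio.

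**Step 4. Two routes to a pass at slow pace**, each assuming that retention and attendance are satisfactory.

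- *Recruitment continues until 75 are enrolled.* At 48 months the consent ratio is still 75/150 = 50%. Retention and attendance are then judged on 75 dyads exactly as planned, and the count of 54 is no obstacle.
- *Recruitment closes at month 24.* With 38 of 75 eligible dyads consenting, the ratio is 38/75 = 51%, which passes. If 27 of the 38 complete, 27/38 = 71%, which passes a percentage rule. It fails if 54 is an absolute count, since 38 < 54.

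**Step 5. What the count of 54 means.** 70% of 75 is 52.5, so the smallest qualifying whole number is 53; 54/75 is 72%. The count does not follow exactly from the percentage beside it, and the text does not say which governs when fewer than 75 are enrolled.

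**The case against.** The strongest reply is that nothing here is misstated. Accrual can be read as the proportion accrued, the rule makes it measurable, and pace may be covered in the full protocol, which is not shown. The first part stands as far as it goes: this is not a contradiction. But the article sets out its decision rule twice, with the same three thresholds and no element of number or time, so the gap is in the rule as stated. If only consent is meant, the dimension should be called that.

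The second reply is that the count of 54 already protects against slow recruitment. This is partly right. If enrolment closed in April 2020 and the count were absolute, enrolling fewer than 54 dyads would fail. It does not act when recruitment is extended, and the wording supports a percentage reading at least as well.

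Three stronger readings are tempting, and the documents support none of them:

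- A reader might infer that slow recruitment would certainly be declared feasible. It would not: that depends on the reading of the count, on whether recruitment is extended, and on retention and attendance.
- A reader might infer from the eligibility criteria, such as the requirement to "have a Karnofsky Performance Status (KPS) of 80 or more", that eligible dyads are the bottleneck. No site volume is given. Both low-grade and high-grade tumors are covered, and the caregiver may be any of several relatives.
- A reader might infer that the larger trial could not be completed. Its size, sites and eligibility are undefined, so pace in this trial does not settle that.

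A further fair objection is that a hard line at 3.1 per month would be too strict, because 74 dyads in 24 months (74 / 24 = 3.08) would fail. That stands, and it is why a tolerance is needed.

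**Conclusion.** The point holds in a limited form. Accrual is named as a dimension of the primary objective, but the rule that represents it does not depend on how many dyads are enrolled or how quickly. A trial enrolling at half the planned pace could meet all three criteria if recruitment were extended to about 48 months, or if it closed at 24 months with about 38 dyads and retention were taken as a percentage of those enrolled. Both cases assume consent of about 50%, at least 70% completion and at least 50% average attendance.

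The planned pace of 3.1 to 3.3 dyads per month follows from the sponsor's own target and window. The slower paces are illustrations only. This is a cheap improvement to the decision rule; it does not invalidate the design or the other criteria.

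**What to change.** In Specific aim 1:

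1. Add an accrual criterion tied to the existing figures: 75 dyads randomized within the stated window (about 3.1 per month over 24 months, 3.3 over 23), with a tolerance that the sponsor fixes before accrual data are reviewed. As an example, 80% gives 0.8 × 75 = 60 dyads in the window, or 60 / 24 = 2.5 per month. The 80% is illustrative; the sponsor should justify its own value.
2. State whether 54 is an absolute count or an illustration of 70% of 75, and correct it to 53 if the latter.
3. Report the numbers screened, eligible and randomized per month beside the consent rate.

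If no such criterion is wanted, the minimum is to rename the dimension as consent rate, so that the verdict does not claim to cover accrual.

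**Cost.** The verdict becomes slightly harder to pass. A simple screening log is needed: the Feasibility section under Study measures lists consent rates with refusal reasons, attrition, attendance and questionnaire completion, but not monthly screening counts or enrolment dates. Because recruitment started in May 2018, the new criterion would be added to the primary outcome of a trial already under way. It must be dated and disclosed as an amendment, with a statement of what was known about accrual when it was set.

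### The retention criterion gives two different pass marks: 70% of the planned 75 dyads is 53, but the count printed beside it is 54 (72%)

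*Protocol article*

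**What the plan says.** The protocol article, Statistical methods, Specific aim 1, sets the lines by which the trial is judged feasible. On retention it says "we will deem the trial feasible if at least 70% of enrolled dyads", and attaches a count in parentheses, at least "54) are retained and complete all follow-up assessments". The abstract repeats the 70% but gives no count.

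The planned total is stated under Sample size and sample size considerations: "We will randomize 75 dyads to either the DY intervention, CY, or WLC groups (25 dyads per group"). The abstract and Specific aim 1 also use 75. No other total appears.

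On consent, Specific aim 1 requires that "at least 50% of eligible dyads consent to participate", and explains this in parentheses as "approach 150 couples to accrue 75". Recruitment describes the order of events: "We will approach potential participants during their initial RT consult or RT simulation visits (prior to starting RT), screen them for eligibility", after which consent is sought.

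**The concern.** A percentage and a count printed as the same rule should give the same verdict for every possible result. Here they do not: the count corresponds to a higher percentage than the one beside it. This is a pass/fail line on the primary outcome. The statistical section says that its steps determine whether the two yoga programmes go forward to a larger trial, and the Discussion says that missing the criteria would move the trial to later points in the treatment trajectory. With two cut-offs in one sentence, the verdict at the boundary could be chosen after the data are seen.

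The consent criterion raises a lesser question. Its parenthesis counts couples approached, while the criterion counts eligible dyads. Recruitment places approach before eligibility screening, so those approached can include dyads who turn out to be ineligible.

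**Working it through.** **Inputs**

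- Planned dyads, N = 75 (Sample size; abstract; Specific aim 1).
- Retention threshold: 70%, with printed count 54 (Specific aim 1).
- Consent threshold: 50% of eligible dyads, illustrated as 75 from 150 (Specific aim 1).
- True retention and the share of approached dyads who are eligible are not given. The values used below are assumptions.

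**Can 54 be reproduced?** The required count is the smallest whole number r with r/N ≥ 0.70.

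- 0.70 × 75 = 52.5, so r = 53.
- 52/75 = 69.3% (fails), 53/75 = 70.7% (passes), 54/75 = 72.0%.
- Rounding 52.5 either way gives 52 or 53, never 54.

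**For which N is 54 the 70% count?**

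- N = 74: 51.8, so 52
- N = 75: 52.5, so 53
- N = 76: 53.2, so 54
- N = 77: 53.9, so 54
- N = 78: 54.6, so 55

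Only 76 or 77 enrolled dyads give 54, and neither number appears in the article.

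**How often would the two rules disagree?** They conflict only when X, the number of completing dyads, is exactly 53. Taking X as binomial (75, p), with dyads independent and a common retention probability p, P(X = 53) = P(X ≥ 53) − P(X ≥ 54):

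| Assumed true retention p | Pass with 53 or more | Pass with 54 or more | Conflict (exactly 53) |
|---|---|---|---|
| 65% | 18.3% | 12.4% | 5.8% |
| 70% | 50.7% | 40.7% | 10.0% |
| 75% | 84.2% | 77.1% | 7.0% |
| 80% | 98.1% | 96.5% | 1.6% |

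**Consent.** 75/0.50 = 150, so the plan's figure reproduces exactly if all 150 are eligible. If only a share e of those approached is eligible, 150 approached contain 150e eligible dyads, and the 50% rule needs half of these to consent. Reaching 75 consents at exactly 50% of eligible then takes 150/e approaches:

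| Assumed e | Eligible among 150 approached | Consents needed for 50% of eligible | Approaches for 75 consents at 50% |
|---|---|---|---|
| 0.9 | 135 | 68 (67.5 rounded up) | 167 |
| 0.8 | 120 | 60 | 188 |
| 0.7 | 105 | 53 (52.5 rounded up) | 215 |

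At e = 0.8, for example, 60 to 74 consents from 150 approached would meet the stated criterion but fall short of the 75 in the parenthesis. In the other direction, 75 consents from 150 approached always satisfy the 50%-of-eligible rule.

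**The case against.** The strongest reply on retention is that the slip is small and safe. It is one dyad, it matters at one result only, and it errs on the strict side, so it cannot declare feasible a trial that retained less than 70%. The percentage is the same in the abstract and the methods, so a reader has an obvious governing rule, and rates will be reported with 90% confidence intervals. The 10% figure is also the largest of the four shown, because it takes true retention to lie on the threshold. All of this stands and limits the size of the point. It does not make 54 the right count for 75, nor does the article say which of the two governs.

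It might also be said that 76 or 77 dyads could be enrolled, for instance if a few consented and were lost before randomization, since baseline assessment comes first. That is possible, but no such number is stated, and Specific aim 1 itself speaks of accruing 75. How dyads lost between consent and randomization are counted is detail that an article may leave to the full protocol, so no fault is claimed there.

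On consent, a reader might infer that the 150 is also a wrong count, or that the protocol sets a second pass mark at half of those approached, which could fail a trial that meets its own criterion. The article does not support this. The arithmetic is exact, the criterion is stated on eligible dyads in both the abstract and the methods, and the parenthesis can be read as eligible dyads approached. No eligibility rate is given, and staff first identify candidates through the appointment system, so the size of any gap is unknown. What remains is a loose denominator in an explanatory aside.

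**Conclusion.** The retention criterion is wrong as written. With the planned 75 dyads, 70% means at least 53; the printed 54 is a 72% rule. The two give opposite verdicts at exactly 53 completing dyads. Under the binomial assumption the chance of that result is about 10% at true retention of 70%, about 7% at 75%, and between 1.6% and 10.0% over the four assumed values from 65% to 80%. The arithmetic rests only on the stated total of 75; the probabilities rest on assumed retention rates.

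The effect is narrow and conservative, but it falls on a decision line of the primary outcome and should be corrected. The consent threshold is arithmetically sound, and only the wording of its parenthesis needs tidying.

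**What to change.** In Specific aim 1, change the parenthesis after the 70% criterion from ≥ 54 to ≥ 53 of 75, and add that the percentage governs if the number of enrolled dyads is not exactly 75.

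As a secondary edit, reword the consent parenthesis so that it refers to 150 eligible dyads rather than to couples approached.

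Both are wording changes to one paragraph. They need no new data, change neither the sample size nor the stated percentages, and leave the analysis as it is. The retention correction should be recorded before the completion count is known, so that it cannot appear to have been prompted by the result.

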#### Exploratory aim

As an exploratory aim, we will explore descriptive analyses including cross-sectional and prospective correlations of measures of medical and demographic factors (e.g., grade and age) and psychosocial factors (e.g., baseline CES-D scores) [80]. We will also explore a dose effect examining if class attendance and home practice are associated with QOL measures. We will explore if delivery (i.e., hospital versus videoconferencing) is associated with differential outcomes. These results will inform optimal dosing of the yoga program in the larger study. Additionally, we will calculate the intraclass coefficients for patient and FCG variables to further provide a rationale for this dyadic intervention.

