## Methods

### Design overview and study setting

The design will involve a feasibility randomized controlled trial with parallel allocation. Caregiver-patient dyads will complete the initial self-report assessments, and then be randomized to the DY, CY, or WLC groups. Follow-up assessments will be completed within 1 week of finishing RT and again 3 months later. For each completed questionnaire, participants will receive a $20 gift card ($60 per participant). Participants’ parking costs for yoga session appointments will be paid if they are not covered by the hospital. Participants in the DY and CY intervention groups will attend 15 sessions (60 min each) over the course of patients’ 6-week standard RT (2–3 sessions per week). Dyads in the WLC group will receive usual care. Sessions 1–4 are delivered in person in a room designated for behavioral interventions, which is located near the RT treatment area. For sessions 5–15, participants will have the option to continue to attend the sessions at the hospital or receive the sessions via HIPAA compliant videoconferencing delivery (e.g., Facetime, Zoom). For participants who have internet access but no electronic device and would like to use videoconferencing, we will loan an iPad for the course of the intervention period.

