### Interventions

#### Dose

Participants in both groups will receive practice sessions 2-3 days per week over the course of standard 6-weeks RT (15 sessions total, 45 min each).

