#### Home practice

Participants in both yoga groups will receive a DVD, URL information to access electronic video files, and printed materials and will be encouraged to practice together (DY group) or individually (CY group) on days when they do not meet with the instructor and asked to keep a practice diary to be turned in on a weekly basis. Participants in the CY group are asked on a weekly basis if patients participated in their home practice to assess for patient contamination.

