#### Feasibility

Consent rates including refusal reasons, study attrition, class attendance, and completion of each questionnaire will be documented. We will document if participants attended sessions 5–15 at the hospital or via videoconference delivery including reasons for their preference. For those choosing videoconference delivery, we will record if they use their own or a loaner device. Participants in the yoga arms will be asked to complete paper-pencil practice logs of their home practice, and if they practiced together or alone (dyads in the DY group) and shared the intervention content with others (CY group), which will be submitted to the instructor on a weekly basis. After the last session is completed, using Redcap, participants in the yoga arms will be asked to identify aspects of the program they like or dislike, identify what they find most and least useful, communicate whether they perceive any benefit from the yoga program, and rate their interventionist.

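### Associations of QOL with self-selected attendance, home practice and delivery mode cannot identify an optimal dose, yet the exploratory aim says they will inform it

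*Protocol article*

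**What the plan says.** All references are to the protocol article. Under Statistical methods, Exploratory aim, the first relevant statement is "We will also explore a dose effect examining if class attendance and home practice are associated with QOL measures". The next is "We will explore if delivery (i.e., hospital versus videoconferencing) is associated with differential outcomes". The use of both follows directly: "These results will inform optimal dosing of the yoga program in the larger study".

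Other sections show how these exposures arise:

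- **Planned dose.** Under Dose, "Participants in both groups will receive practice sessions 2-3 days per week over the course of standard 6-weeks RT", 15 sessions in total. DY and CY share this schedule, and no arm is assigned a different number of sessions.
- **Home practice.** Participants "will be encouraged to practice together (DY group) or individually (CY group) on days when they do not meet with the instructor" and record it in a diary (Home practice).
- **Delivery.** From the fifth session on, the mode is left to choice: "participants will have the option to continue to attend the sessions at the hospital or receive the sessions via HIPAA compliant videoconferencing delivery" (Design overview and study setting). Under Feasibility it is recorded as a preference: "We will document if participants attended sessions 5–15 at the hospital or via videoconference delivery including reasons for their preference".

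Minimization is on sex, age, tumor grade and KPS, and it assigns dyads to arms (Randomization). The Discussion declines to examine effect sizes from this trial on the ground that they could mislead.

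**The concern.** A dose effect is a causal claim: more sessions or more practice lead to better QOL. Under a single planned dose, the contrast is between people who attended or practised more and people who did so less. Sessions run during the 6 weeks of radiotherapy, and the first follow-up falls within 1 week of its end. A dyad whose patient tolerates treatment badly could miss sessions and also report worse QOL, whatever yoga does. Balance between arms on KPS and grade gives no balance between high and low attenders, or between hospital and video users, within the yoga arms.

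Delivery raises the same difficulty, since it is chosen by the participant. It is also not a dose, so a comparison of delivery modes says nothing about how much yoga to give.

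What is at stake is the design of the larger trial. If an association of this kind weighs in the choice of dose, that choice may partly reflect who was well enough, or free enough, to attend.

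**Working it through.** The plan gives no figure for this analysis, so there is none to reproduce. The check has four steps.

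**1. Who has the exposure.** There are 25 dyads per group, so at most 25 + 25 = 50 caregivers have a class-attendance exposure. CY caregivers are taught without the patient, so only the 25 DY patients have a class-attendance exposure of their own. At the plan's 70% retention threshold these become 0.70 × 50 = 35 caregivers and 0.70 × 25 = 17.5, about 18, patients.

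**2. Association expected with no dose effect.** Let one health variable correlate *a* with attendance and *b* with QOL, and let attendance have no effect on QOL. The induced correlation is r = a × b. The values of *a* and *b* are assumptions, since the documents give none.

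| a = b | a × b | Simulated mean r, n = 50 | Simulated mean r, n = 35 |
|---|---|---|---|
| 0.3 | 0.09 | 0.089 | 0.088 |
| 0.5 | 0.25 | 0.247 | 0.246 |
| 0.7 | 0.49 | 0.485 | 0.485 |

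The simulation used 20,000 replicates per setting. Mixed pairs fall between: 0.3 × 0.7 = 0.21 and 0.5 × 0.7 = 0.35. The result thus runs from negligible to large, depending on inputs nobody knows.

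For delivery, suppose healthier participants tend to choose the hospital, with a 50/50 split and no true delivery effect. The expected difference in QOL is 2ab√(2/π) ≈ 1.6ab in SD units: 0.14, 0.40 and 0.78 for a = b = 0.3, 0.5 and 0.7. Simulation (4,000 replicates) gave 0.15, 0.40 and 0.78.

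**3. Precision.** For an observed r of 0.3, the 95% interval is tanh(atanh 0.3 ± 1.96/√(n − 3)):

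- n = 50: 0.02 to 0.53
- n = 35: −0.04 to 0.58
- n = 25: 0.310 ± 0.418 on the z scale, so −0.11 to 0.62

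Even without confounding, these samples could not separate a weak relation from a strong one.

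**4. What baseline adjustment can do.** Suppose the baseline measure correlates ρ with health during radiotherapy, and acts on attendance and QOL only through it. After adjustment, the covariance left is ab − (aρ)(bρ) = ab(1 − ρ²). This is zero only if ρ = 1, that is, if baseline status fully determines health over the 6 weeks. Adjustment is worth doing, but it leaves the part due to deterioration after baseline.

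**The case against.** A reader might infer that the plan will set the dose of the larger trial from crude correlations known to be confounded. The document does not support that reading:

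- **Set.** The text says the results will inform dosing. It stands under an exploratory aim, with no decision rule or threshold.
- **Crude.** The article neither specifies nor excludes adjustment. It condenses a fuller protocol, and an analysis plan not shown could add covariates. Silence on adjustment is therefore not the finding.
- **Confounded as a fact.** No data on this are given. Entry requires a KPS of at least 80, which narrows the range of patient health. Patients come in for daily radiotherapy and the yoga room is near the treatment area, so travel is a weaker reason for patients to choose video. The video option and loaner devices make attendance less dependent on being able to come in. In CY only the caregiver attends, and a burdened caregiver might attend more or less, so even the direction is open.
- **False-positive rates.** The plan names no significance test here, so a rejection rate would describe a test it does not propose. The size is therefore given as a correlation, over a range.
- **Delivery.** The Discussion ties delivery to participants' preference, which is a sound descriptive use of the recorded reasons.

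All of this stands, and it limits the point. It does not rescue the dosing sentence, which is a stated inference rather than an omitted detail. With one planned dose and self-selected exposure, adjustment in an unseen plan would not turn attendance into a dose comparison. The exploratory label also sits uneasily with the design role that the same paragraph gives the results, and with the Discussion's caution about effect sizes.

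**Conclusion.** The point holds in limited form. The associations may be explored, but they cannot identify an optimal dose, because every yoga participant has the same planned 15 sessions and the exposures are self-selected after randomization. This conclusion follows from the design and needs no assumed number.

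The size of any confounding does rest on assumptions. With one health variable and no true dose effect, the induced correlation is about 0.09 at the low end of the assumed range, 0.25 in the middle and 0.49 at the high end. The low end would matter little. The middle and high end could pass for a real dose-response.

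Severity is modest. The aim is exploratory, and neither the primary feasibility outcome nor the descriptive second aim is affected.

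**What to change.** 1. Replace the optimal-dosing sentence with wording such as: these associations are hypothesis-generating and do not by themselves determine dose or delivery in the larger study. Describe the analysis as an association with attendance and practice rather than a dose effect.
2. Estimate the attendance, home-practice and delivery associations adjusted at least for the baseline value of the same outcome, and for KPS and tumor grade where numbers allow. Do this separately for patients and caregivers. Only the 25 DY patients have a patient class-attendance exposure, about 18 at 70% retention, so keep covariates few there.
3. State that baseline adjustment does not remove confounding by deterioration during radiotherapy.
4. Base statements about what the larger study can deliver on the attendance records and the reasons for delivery preference, which the Feasibility section already collects.

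The cost is a few lines of wording and a few degrees of freedom, which are felt most in the patient models. Baseline outcomes, KPS and grade are already available, so no new measurement is needed.
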